### Model definition

The model is conceptualized as a developmental delivery architecture wherein human counselors establish the relational frame and developmental arc, while AI system executes the high-frequency micro-dosage required for proximal skill enactment. Critically, this intervention does not conceptualize AI as a counselor analog, therapist substitute, or diagnostic component, but as a systemic dosage amplifier. Counselors maintain primary responsibility for relational containment, while the AI autonomously delivers the high-volume, micro–developmental practice opportunities that human counselors cannot feasibly scale. This approach is grounded in the developmental reality that self-regulation and social connectedness are not cultivated through episodic learning, but through continuous, real-world repetition. The architecture therefore mirrors the mechanisms of motor-skill acquisition: micro-practice → consolidation → transfer. This counselor–AI co-delivery framework makes this repetition feasible within standard school constraints.

The intervention is deployed throughout eight consecutive school weeks. Each week focuses on one thematic developmental objective (see Table 1) and offers a synchronous 10–15-min counselor mini-session. This mini session serves as a vital “anchor point,” grounding the week’s developmental target in a supportive relational context while allowing the counselor to check ecological fit, safety, and progress. The remainder of the weekly dosage is delivered digitally through daily MI-style micro-nudges (e.g., ≤ 40 words). The sequence is intentionally graded to build capacity over time: initial weeks emphasize foundational awareness and micro-choice recognition; intermediate weeks prioritize active skill application in real-life contexts; final weeks focus on value mapping, identity congruence, and future transfer. In essence, the intervention is paced not by superficial “topic rotation,” but through the cumulative scaffolding of practice complexity.

**Table 1 tab1:** Structured eight-week progression of developmental objectives and measurable indicators.

Week	Theme	Weekly skill focus	Measurable outcome wording	Measurement schedule
0				Weeks −2 to −1: Consent, demographics, BSCS/SSBS (pre), two-week daily EMA baseline (Phase A)
1	Awareness	Noticing internal states & situational triggers	Student(s) can label at least one emotional state + one situational trigger per day	

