## Method

### Setting and participants

The intervention is designed for implementationwithin mainstream high school counseling settings serving adolescents aged 14–18. This ecological frame is intentional. As a feasibility study, the sample size is determined by the need to evaluate implementation applicability and estimation precision rather than statistical power for clinical efficacy. A target sample of 40–60 students from routine school caseloads, is sufficient to yield narrow confidence intervals (CIs) for recruitment/retention/compliance and to visualize heterogeneous individual-level micro-trajectories within an authentic delivery context. Feasibility will be evaluated against four pre-specified operational thresholds: (a) a recruitment rate ≥ 70% of eligible students; (b) a retention rate of ≥ 80% (defined as completing both pre- and post-intervention trait measures); (c) a median EMA compliance of ≥ 60% for daily prompts (1–7 Likert scale) across Weeks 1–8; (d) an intervention fidelity of ≥ 75% (defined as weeks where all three checklist items are met). These thresholds were derived from established benchmarks in the feasibility and pilot trial literature (Billingham et al., 2013; Eldridge et al., 2016). The 70% recruitment and 80% retention rates are widely adopted as minimum indicators of a viable study pipeline for a subsequent full-scale trial. The 60% EMA compliance threshold reflects the empirically observed lower bound of acceptable ecological momentary data completeness in adolescent digital health studies (Shiffman et al., 2008); compliance below this level produces phase lengths insufficient for reliable Tau-U estimation. The 75% fidelity threshold is grounded in the intervention science literature’s recommendation that at least three-quarters of protocol sessions be delivered as specified before efficacy conclusions can be considered (Bellg et al., 2004). Together, these benchmarks ensure that a positive feasibility verdict is substantively meaningful rather than nominally so.

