Momentary (state-level) regulations will be assessed through a daily, single-item Ecological Momentary Assessment (EMA) self-rating prompt delivered throughout the eight-week intervention phase. Adolescents are prompted with the question: “Right now, how effectively are you managing your emotions and behavior?” and respond on a 1–7 Likert scale (1 = *not effectively at all*, 7 = *very effectively*). Basically, this item is designed to capture real-time regulatory enactment rather than a retrospective or global self-assessment. Thus, EMA state trajectories recorded across Phase B provide a mechanism-level time-series dataset optimally structured for single-case Tau-U analysis.

All outcome indicators depend on student self-report, the protocol also incorporates two additional informant-based measures. Teacher behavioral ratings will be collected at pre- and post-intervention timepoints using a brief four-item adaptation of the Social Skills Improvement System (SSIS; Elliott et al., 2008) targeting observable classroom regulation behaviors (e.g., “This student recovers quickly from frustration”) and prosocial conduct (e.g., “This student initiates positive interactions with peers”). Items are rated on a 4-point frequency scale (1 = never, 4 = almost always) by the student’s primary classroom teacher. Parent or guardian reports will be collected using a parallel four-item brief form targeting home-context regulation and social behavior, administered via a secure online survey link at the same two timepoints. These informant sources provide convergent evidence from ecologically distinct observational contexts, reducing the sole reliance on student self-report and mitigating single-source inflation of perceived effects.

Implementation of fidelity will be captured via weekly counselor fidelity summaries. To minimize administrative burden and avoid interpretive drift, this documentation uses a structured, three-item binary checklist. The counselor simply records whether: (1) micro-nudges were opened at least four times during the week; (2) the student submitted at least one reflective note; and (3) the student concretely described at least one pro-social or regulation-aligned behavior. Counselors may optionally add a single-sentence contextual remark if relevant. These logs do not serve as qualitative data for phenomenology, but rather as direct fidelity evidence confirming that the designed mechanism was actively enacted.

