Quantitatively, the design combines a within-subject trait-level pre–post comparison with an embedded single-case AB probe. The sequence consists of a pre-intervention baseline (Phase A; Weeks −2 and −1) and an active intervention period (Phase B; Weeks 1–8). The two-week baseline was adopted. A minimum of 10 data points in Phase A provides a more stable trend estimate for Tau-U baseline correction and more clearly distinguishes pre-existing directional drift from intervention-related change. Throughout Phase B, state-level EMA micro-ratings (1–7 Likert scales) index continuously index momentary regulation states. Trait-level self-regulation and social connectedness are measured at pre- and post-intervention timepoints via the within-subject standardized mean difference (Cohen’s *d*). To rigorously capture the dynamics of the state-level micro-trajectories, data will be evaluated using Tau-U, a robust, best-practice non-overlap effect size optimized for AB sequences in single-case experimental design (SCED) methodology.

The qualitative strand consists of (a) weekly counselor fidelity logs and (b) brief, one-sentence reflective student notes. These materials are not narrative interviews; rather, they serve as real-time process-evidence. Therefore, the analytic objective is not to achieve thematic saturation, but to execute mechanism-alignment detection. Reflexive thematic analysis will be used to identify and verify whether developmental practice indicators outlined in Table 1 occurred within a real-world educational environment.

All reflective notes remain accessible to the counselor to preserve the core ethical principle of human relational containment. The AI system does not store raw text beyond the generation of summary logs. Data retention adheres strictly minimal-retention feasibility norms; export functions are disabled. No participant data or conversational data is used for model training or model improvement. Furthermore, no algorithmic action is permitted without the possibility of immediate human override; should emotional dysregulation signals emerge, counselors escalate the case in accordance with established institutional safeguarding protocols. In this design, the AI is never the locus of clinical decision; rather, it is the engine for prompt density. Human counselors retain absolute safeguarding authority and interpretive control.

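### The 60% EMA compliance threshold is justified by Tau-U phase length but counts only Weeks 1–8; no feasibility threshold covers Phase A, the only phase with a stated minimum

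*Protocol article*

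**What the plan says.** The Protocol article, Setting and participants, lists four feasibility thresholds. The third is "a median EMA compliance of ≥ 60% for daily prompts (1–7 Likert scale) across Weeks 1–8". Two reasons are given for 60%: an external benchmark for data completeness in adolescent studies, and the statement that "compliance below this level produces phase lengths insufficient for reliable Tau-U estimation". The retention threshold in the same list is defined on the pre and post trait measures, not on EMA.

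Research design sets out an AB sequence with a "pre-intervention baseline (Phase A; Weeks −2 and −1" and an intervention Phase B in Weeks 1–8. It explains the baseline length thus: "A minimum of 10 data points in Phase A provides a more stable trend estimate for Tau-U baseline correction". Table 1 (Model definition) schedules a "two-week daily EMA baseline (Phase A". Data analysis strategy compares Phase A with Phase B by Tau-U with correction for baseline trend.

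Measures, by contrast, describes the EMA item as a "self-rating prompt delivered throughout the eight-week intervention phase" and does not mention the baseline. Missing data handling drops unanswered days, sets no minimum number of ratings per phase, and reports each student's overall percentage of prompts answered.

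**The concern.** A threshold defended by the needs of an analysis should bind where that analysis is weakest. A trend-corrected AB comparison is weakest in the short phase, because the baseline slope is estimated from Phase A alone. Threshold (c) starts counting at Week 1 and so leaves Phase A out.

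Two things follow. The reason given for 60% may not hold on the plan's own figures. And the study could be declared feasible with a sparse baseline series, although the state-level comparison is one of the three analytic layers it is meant to try out. The article is offered as a template for later trials, so the gap would be copied. Baseline ratings that are not collected before Week 1 cannot be recovered afterwards.

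**Working it through.** **Inputs**
- Threshold: 60%, Weeks 1–8 (Setting and participants).
- Minimum: 10 points in Phase A (Research design).
- Phase A: two weeks (Table 1; Research design). Phase B: eight weeks; "The intervention is deployed throughout eight consecutive school weeks" (Model definition).
- Prompts per phase: not stated. Daily prompting gives 14 and 56 on calendar days, or 10 and 40 on school days. Both are carried through.
- Expected Phase A compliance: not stated. It is treated as an assumption and varied.

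**Step 1. Can 60% be reproduced as the level below which phases become too short?** The compliance needed for 10 ratings is 10 divided by the number of prompts.

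| Phase | Prompts | Needed for 10 ratings | Ratings at 60% |
|---|---|---|---|
| A, calendar days | 14 | 10/14 = 71.4% | 8.4 |
| A, school days | 10 | 10/10 = 100% | 6 |
| B, calendar days | 56 | 10/56 = 17.9% | 33.6 |
| B, school days | 40 | 10/40 = 25% | 24 |

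It cannot. Measured against the only minimum in the document, 60% is far above what Phase B needs and below what Phase A needs, under either schedule.

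**Step 2. Does another threshold cover Phase A?** Recruitment counts enrolment. Retention counts trait questionnaires. Fidelity is a weekly checklist of opened nudges, reflective notes and described behaviours. EMA compliance begins at Week 1. None of them counts Phase A ratings.

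**Step 3. How many students would reach 10 baseline ratings?** Let p be the daily response probability in Phase A, the same for all students and independent by day. For 14 prompts, P(X ≥ 10) = Σ C(14,k) p^k (1−p)^(14−k), summed over k = 10 to 14. For 10 prompts it is p^10; for example, 0.6^10 = 0.006.

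| p | 10 or more of 14 | 10 of 10 |
|---|---|---|
| 0.60 | 27.9% | 0.6% |
| 0.70 | 58.4% | 2.8% |
| 0.80 | 87.0% | 10.7% |
| 0.90 | 99.1% | 34.9% |

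Half the students reach 10 when p is about 0.67 (14 prompts) or 0.93 (10 prompts).

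At p = 0.60 with 14 prompts, 72.1% fall short. In the target sample that is 0.721 × 40 ≈ 29 to 0.721 × 60 ≈ 43 students.

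**Step 4. Sensitivity to differences between students.** If individual compliance follows a beta distribution with median 60% (precision 3 to 20), 33–41% reach 10 of 14 and 2–10% reach 10 of 10. At that median the picture is the same.

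**Step 5. Measures against the schedule.** Measures places the prompt in the eight intervention weeks and presents the Phase B ratings as the series for Tau-U. Table 1, Research design and Data analysis strategy all require a baseline series as well. The passages need to be reconciled.

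**The case against.** A reader might infer that students with fewer than 10 baseline ratings cannot be analysed as planned. The document does not say so. Research design offers 10 points as a reason for a steadier trend estimate, not as a condition of entry, and it can be read as a count of scheduled points, since two school weeks give exactly 10. Missing data handling keeps such students and omits the empty days. A student with 8 baseline ratings is analysed according to plan, with a weaker trend correction.

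A reader might also infer that most students will fall short. That carries the Phase B pass mark over to Phase A. With 14 prompts, most students reach 10 once response exceeds about 67%. The very low school-day figures need both school-day prompting, which is not stated, and 10 read as a count of answered prompts.

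Nor does Measures say that EMA is confined to the intervention. It omits the baseline without denying it, and Table 1 is the schedule that sites would follow, so a missing baseline series is a risk of wording and not a likely outcome.

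Finally, the study is about implementation and disclaims causal inference. The external benchmark may support 60% by itself, and low responders would show up in the per-student compliance report.

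All of this stands, and it limits the consequence. It does not rescue the phase-length reason for 60%, and it does not supply a criterion for Phase A.

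**Conclusion.** The point holds in a limited form. The phase-length justification for 60% fails on the plan's own figures: Phase B would still hold 10 ratings at 17.9% or 25% compliance, whereas Phase A needs 71.4% or 100%. Because no threshold counts Phase A ratings, a positive feasibility verdict is compatible with any level of baseline completeness.

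That conclusion rests only on the document and simple division. How many students would be affected is conditional: it depends on the unstated number of prompts, on Phase A response, which the document does not predict, and on independence between days. Across 60–80% response, the share reaching 10 runs from 28% to 87% with 14 prompts and from 0.6% to 11% with 10. The effect is a less stable baseline correction for the students below the minimum, not the loss of their Tau-U estimates.

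**What to change.** 1. State the number of EMA prompts in each phase, and whether they run on calendar or school days. The other changes depend on this.
2. Reword Measures to agree with Table 1, Research design and Data analysis strategy, so that EMA runs from Week −2 to Week 8.
3. Report compliance separately for Phase A and Phase B.
4. Add a Phase A completeness measure to the feasibility criteria: the share of students with at least 10 baseline ratings, with its target fixed in advance. If prompts run on school days, 10 of 10 requires perfect response, so set a minimum that the schedule can support.
5. Delete or correct the phase-length reason for 60%. The benchmark reason can remain if the authors stand by it.
6. Keep all students in the main Tau-U summary, and show those with at least 10 baseline ratings as a sensitivity analysis. Using 10 as an exclusion rule would select the best compliers and, under school-day prompting, would leave very few students.

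The cost is protocol wording, one extra tabulation and a slightly harder feasibility criterion. The changes should be made before enrolment.

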Participation is voluntary, contingent upon the student’s willingness to engage in daily reflective micro-interactions for 8 weeks. Inclusion criteria are intentionally minimal to maximize ecological validity: must (a) possess sufficient functional literacy to interpret daily reflective prompts, (b) have access to a digital interface (e.g., mobile device), and (c) be available for one weekly 10–15 min synchronous mini-session with a counselor. Exclusion criteria are guided by safety and feasibility logic rather than clinical diagnostics. Students presenting with acute crisis indicators (e.g., active suicidal intent, imminent risk of harm, or major protective disclosure) are not enrolled into this model because such circumstances require immediate professional care with crisis protocols. The purpose of this design is not to triage or treat acute dysregulation but to examine whether an AI-supported PYD scaffold can be realistically implemented within an ordinary school setting.

To ensure participant safety, any Adverse Events (AEs) including disclosures of harm, acute distress, or technology misuse will be monitored, documented, and reported to the responsible researcher within 24 h. AEs trigger immediate counselor escalation in accordance with institutional safeguarding policies; serious AEs are logged and reviewed by the school’s safeguarding lead. The AI system is structurally restricted from issuing behavioral directives; all guidance remains purely reflective and strictly under human counselor’s clinical oversight.

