In addition to the design-level constraints noted above, several AI-specific risks warrant explicit acknowledgment, as these are now priority concerns in educational AI literature. First, LLMs are susceptible to hallucination, meaning the model may occasionally generate factually inaccurate or contextually inappropriate responses. Although the system’s rule-based prompt architecture constrains output to MI-style reflective templates and reduces this risk, it cannot be entirely eliminated. Counselors are therefore instructed to review flagged interactions and to treat any factually dubious AI output as a fidelity concern requiring immediate intervention. Second, algorithmic bias may be present in the underlying model’s training data. Students from minority cultural, linguistic, or socioeconomic backgrounds may encounter prompts that implicitly reflect dominant-cultural norms or fail to resonate within their relational context. The pre-deployment audit described in the AI System Specification section includes sensitivity review by raters with diverse cultural backgrounds; however, residual bias cannot be fully excluded and should be documented during implementation. Third, emotional dependence on the AI system is a theoretically plausible risk, particularly for adolescents experiencing social isolation or acute relational distress. The protocol mitigates this risk structurally by maintaining the weekly counselor mini session as a non-negotiable relational anchor and by ensuring the AI’s role is framed to students as a practice tool rather than a relational agent. Counselors are trained to monitor engagement patterns and to intervene if a student’s interaction frequency suggests substitution of AI contact for peer or counselor relationships. These risks do not invalidate the feasibility rationale of the study, but they underscore the necessity of maintaining robust human oversight throughout the protocol.

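### The adverse-event examples name none of the three AI risks the protocol acknowledges, and dubious AI output is sent to a fidelity record with no item for it

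*Protocol article*

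**What the plan says.** **Adverse events.** Setting and participants states that "any Adverse Events (AEs) including disclosures of harm, acute distress, or technology misuse will be monitored", documented and reported to the responsible researcher within 24 hours. It adds that "AEs trigger immediate counselor escalation in accordance with institutional safeguarding policies". Serious events also go to the school's safeguarding lead for logging and review.

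**AI risks.** The Limitations section acknowledges three risks and gives each its own handling:
- Output: "First, LLMs are susceptible to hallucination, meaning the model may occasionally generate factually inaccurate or contextually inappropriate responses". Counselors review flagged interactions and are to "treat any factually dubious AI output as a fidelity concern requiring immediate intervention".
- Bias: "residual bias cannot be fully excluded and should be documented during implementation".
- Dependence: "Third, emotional dependence on the AI system is a theoretically plausible risk". The response is "Counselors are trained to monitor engagement patterns and to intervene if" a student's pattern of use suggests that AI contact is replacing human contact.

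**Fidelity record.** Under Measures and in Appendix B, the weekly log has three yes/no items: at least four nudges opened, at least one reflective note submitted, and at least one relevant behaviour described. A one-sentence remark is optional. Setting and participants counts a week as faithful when all three items are met and sets the threshold at 75%.

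**What is kept.** AI system specification limits the weekly logs to aggregated counts and engagement summaries and discards dialogue text after the session. Audit logs are kept for the study, and a crisis-keyword match hands the case to the counselor.

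**The concern.** This is a feasibility study of an AI system used by 14- to 18-year-olds. One of the most useful things it can pass to a later trial is a record of how often the AI produced something it should not have, how often a prompt was culturally harmful, and how often counselors had to step in over dependence. The protocol foresees all three, but its stated routes do not clearly lead any of them to a record that would be read as safety information.

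Dubious output is the sharpest case. The protocol does not merely leave its class open. It assigns it to fidelity, and the fidelity instrument described elsewhere in the same article cannot hold it. An incident may be dealt with promptly by a counselor and still leave no trace in either the AE record or the fidelity result.

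The consequence extends beyond this study. The Introduction offers the protocol for direct adaptation by later randomized trials, and Practical contribution lists the human-in-the-loop safety structure among the parts to be transferred. A gap in incident capture would be carried over with it.

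**Working it through.** There is no stated figure to reproduce and no formula to apply. The check sets the sections side by side and counts.

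**Step 1. AI risks against the AE examples and the stated handling**

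| AI risk (Limitations) | Named as an AE example? | Stated handling | Linked to AE reporting? |
|---|---|---|---|
| Inaccurate or inappropriate output | No | Fidelity matter if factually dubious, with immediate intervention | No |
| Algorithmic bias | No | To be documented; no instrument named | No |
| Emotional dependence | No | Counselor monitors and intervenes; no record named | No |

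Named: 0 of 3. Linked to AE reporting: 0 of 3. Sent to fidelity: 1 of 3, and for that one only the factually dubious kind of output.

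**Step 2. Can the fidelity record hold what is sent to it?**
The three items record nudges opened, a note submitted and a behaviour described. Each is something the student did. Items able to record an AI output: 0 of 3. The optional remark is the only place left, and nothing requires its use.

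**Step 3. Effect on the fidelity result**
A week is scored only on those three items, so a faulty output does not change its score. At the logical limit, a student with a faulty output in every week who met all items would score 8/8 = 100%, against a threshold of 75%. This shows that the measure is insensitive to AI output. It is not a forecast.

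**Step 4. Could the event be recovered later?**
- The counselor's dashboard shows aggregated weekly summaries, and the text is gone after the session.
- Audit logs are retained, but the article does not say whether they contain output text.
- The detection tools described are banned-topic filters and crisis keywords. Neither is described as finding factually dubious or biased output.

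Recovery is possible through the audit logs, but the text does not assure it.

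**Step 5. What does reach the AE record?**
Acute distress is a named example. If a student is visibly distressed after a bad output, a biased prompt or over-reliance, the distress is reportable whatever its cause. The uncaptured events are those without such distress, together with the AI element of those that are captured, because no field records it.

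**The case against.** The strongest reply has five parts.

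1. **The list is open.** The word *including* makes the three items examples. The AI risks are unnamed, and no section says that an AI-related event cannot be an AE. This stands.
2. **Acute distress is already covered.** It catches the AI failures that visibly distress a student, and keyword handoff and counselor oversight add to it. This stands for distress, but not for incidents without it.
3. **A faulty sentence is a hazard and not yet a harm.** Sending every dubious output through AE reporting would count faults that hurt no one. Because AEs trigger immediate escalation, it would also alter how students are managed. This stands, and it is why the fix below uses a separate class.
4. **No safety rate is planned.** The four feasibility thresholds and the three analysed outcomes contain no AE measure. This stands, so no distorted safety estimate can be demonstrated.
5. **An article condenses a fuller protocol.** Detailed AE definitions may sit there. This is fair for the missing detail. It does not answer a classification that the article itself makes and that its own fidelity log cannot carry out.

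A reader might go further and infer that the AE record counts things that are not harms while staying at zero when the AI misbehaves. The documents support neither half. A disclosure of harm is a proper safety event even when the intervention did not cause it, and misuse can be harmful. Acute distress means the record need not stay at zero. What can fairly be said is that the text does not separate problems the programme detects from problems the AI produces.

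**Conclusion.** The point holds as a mismatch between sections. Of the three acknowledged AI risks, none is named among the AE examples and none is linked to AE reporting. The one sent to fidelity meets an instrument in which 0 of 3 items can record it. An AI incident without acute distress may therefore appear in neither the AE record nor the fidelity result.

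No number of missed events can be derived, because the article gives no expected incident rate. The conclusion rests on two readings: that the fidelity log is the three-item checklist in Measures and Appendix B, and that the audit logs, whose content is not described, are not already an incident record. If a fuller protocol defines such a record, the remaining task is to align the article with it. The matter should be settled before enrolment, since discarded dialogue cannot be reviewed afterwards. It does not undermine the study's other aims.

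**What to change.** Reconcile Setting and participants, Measures with Appendix B, AI system specification, and Limitations as follows:

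- **Define a separate class of AI-related incidents:** dubious or inappropriate output; a biased or culturally harmful prompt; counselor intervention for suspected dependence; and acute distress following an AI contact. The last remains an AE as well and is cross-referenced. *Following* should be read as timing, since the design does not support causal attribution.
- **Give it a place on the form.** Add one field to the counselor log for the incident type, kept outside the three items that score fidelity, and require notification to the responsible researcher.
- **Align the wording.** Limitations should point to this record for all three risks, and AI system specification should say what the audit logs retain to support it.
- **Report it apart.** Tabulate AI-related incidents separately from safeguarding disclosures and technology misuse, both of which stay recorded as AEs.

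Escalation and other clinical handling stay as the sponsor sets them; the change concerns recording and reporting only. The cost is a few sentences of protocol text, one more log field for counselors, and a reported AI-incident count that will look less favourable than having none.
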